## Abstract

**Background:**

Anterior knee pain is often reported following intramedullary nailing of tibial shaft fractures. The aetiology remains unclear, but the surgical approach may play an important role. To date, no biomechanically validated method exists to assess patient outcomes specific to anterior knee pain in this cohort. The central aims of this study are to (1) evaluate the feasibility of a full-scale randomised controlled trial (RCT) investigating the influence of surgical approach on intramedullary nailing of tibial shaft fractures (suprapatellar versus infrapatellar nailing), (2) explore differences in clinical outcomes between the approaches, and (3) explore the development of a biomechanically validated methodology for assessing post-operative anterior knee pain and knee function specific to intramedullary nailing of tibial shaft fractures.

**Methods:**

This pilot study will follow a prospective randomised controlled design at the Royal Adelaide Hospital and The Queen Elizabeth Hospital (South Australia). This study aims to recruit 60 patients between 18 and 60 years old who will be randomly assigned to either the suprapatellar or infrapatellar approach following a decision for intramedullary surgical fixation by the treating surgeon. All nails in this study will be Stryker T2 Alpha nails. Patients will undergo standard radiograph, magnetic resonance imaging, and clinical assessments in-line with their standard operative care, and complete a number of patient-reported and performance-based outcome measures. Performance-based outcome measures will be assessed utilising three-dimensional motion capture techniques. Follow-up time points are 3, 6, 12, and 18 months. Feasibility outcomes include ability to meet enrolment and retention metrics, compliance with all questionnaires and assessment procedures, and the occurrence of any adverse events. The primary clinical outcome is the incidence of anterior knee pain at 12 months after surgery.

**Discussion:**

This study will establish the feasibility and inform the design of a large-scale RCT. Evaluation of all clinical data and patient outcomes will lead to the development of a new tool for assessing patient outcomes in this cohort. Limitations of the study include an unpredictable enrolment rate and loss to follow-up, small sample size, and the unknown ability of three-dimensional motion analysis to pick up the effects of anterior knee pain after tibial nailing.

**Trial registration:**

This trial was prospectively registered on the 7 February 2020 on ANZCTR, ACTRN12620000109909.

## Introduction

### Background and rationale

Tibial shaft fractures are the most common long bone fracture [1]. Intramedullary (IM) nailing—the insertion of a surgical nail along the medullary cavity—is commonly used to stabilise these fractures as it enables stable fixation with minimal soft-tissue damage [2]. IM nailing approaches are generally categorised by the nail entry site: infrapatellar nailing (IPN) is performed transtendinous, or by lateral or medial parapatellar approaches, with the knee in a flexed or hyper-flexed position [3, 4]; conversely, suprapatellar nailing (SPN) is an intra-articular technique allowing the knee to remain in near full extension [5]. The promising results of SPN, especially for proximal third fractures, involved in 5–11% of all cases [6], have led some surgeons to adopt SPN as their standard technique [7], and some authors have recommended SPN for treating all fractures of the tibial shaft [8]. However, there is no conclusive evidence to inform surgical decision making on whether an optimal IM nailing technique exists. The choice of approach is typically based on surgeon experience first, and secondarily the fracture pattern. The absence of biomechanically validated in vivo outcome measures specific to this cohort has led to conflicting studies reporting significant differences between SPN and IPN, while other studies have reported no difference in patient satisfaction [9].

One well-documented disadvantage of IM nailing is long-term anterior knee pain (AKP), occurring in 10% [10] to 86% of cases [11]. AKP post-SPN has been reported as non-existent [5], significantly lower than IPN [8], and not different to IPN [12–15]. These differences may in part be explained by differing study designs and the range of scoring systems used being developed for various other knee pathologies [16–19]. AKP can severely influence long-term activities of daily living [20–22], of which, kneeling causes the most severe knee pain [23], and exacerbates existing pain in 60% of cases [24]. This has potentially significant effects for occupations that require kneeling, as well as some religious activities. The incidence of knee pain resulting from kneeling varies [11, 23, 25, 26] but is reported to be as high as 91.8% [27]. Further, 26 [28] to 50% [27] of patients are unable to kneel at all. Two different forms of kneeling have been described: upright and flexed [29, 30]. This results in different anatomical structures contacting the ground [30] which is likely to influence the incidence of AKP. In order to assess kneeling ability, it is important to consider both forms [31]. To date, there have been four randomised, prospective trials looking at SPN versus IPN [8, 14, 32, 33]; only one study [33] assessed kneeling ability but failed to differentiate between kneeling modalities. No research has explored how biomechanical changes in kneeling might relate to AKP after IM nailing.

Using existing patient-reported outcome measures (PROMs), studies have showed that SPN has similar [2, 23] or better [34] functional outcomes when compared to IPN, yet outcomes based solely from PROMs may not be truly representative. A combination of PROMs and performance-based outcome measures (PBOMS) is required to capture patient recovery adequately. Subjective PROMs do not capture information about the mechanics of the tasks being assessed and have not been biomechanically validated for this patient group. Changes in objectively measured gait biomechanics have been evaluated with patient-perceived outcomes following total knee arthroplasty [35, 36], but no studies have attempted to identify important gait- or task-specific parameters associated with tibial shaft fracture patients treated with IM nailing. The correlation of subjective, self-reported assessments of function and pain with the biomechanics of these activities may provide valuable insight into causes of AKP and restricted functional ability.

This pilot RCT will help to establish the basis for a future large-scale RCT and will explore the outcomes of SPN versus IPN through analyses of the biomechanics of different tasks and the evaluation of these findings with AKP and function questionnaires. Important surgical outcomes, such as tibial alignment, fracture union, and intra-articular damage, will also be captured in this study. It is anticipated that the development of biomechanically validated outcome measures used in a full-scale RCT will enable new guidelines for the treatment of tibial shaft fractures to be developed, as well as novel outcome measures specific to this patient group.

## Objectives

### Primary objective

The primary objective of this study is to determine the feasibility of a full-scale RCT, the aim of which is to investigate differences in patient outcomes between the surgical management of tibial shaft fractures treated with suprapatellar versus infrapatellar intramedullary nailing approaches.

### Secondary objectives

We aim to compare the effect of SPN versus IPN with the incidence of AKP and knee function at 3, 6, 12, and 18 months follow-up, utilising a series of patient-reported outcomes and laboratory-based assessments.

### Tertiary objectives

The tertiary objective of the study is to explore the development of novel three-dimensional (3-D) motion capture based biomechanical outcome measures for assessing AKP and knee function after tibial fracture surgery. This will be achieved by evaluating objectively measured biomechanical outcomes and gait patterns against patient-reported outcome measures of knee pain and function.

Additional objectives include comparing the effect of SPN versus IPN on surgical outcomes including: tibial alignment, rotational profile, intra-articular damage, and time to union.

## Methods and analysis

This protocol was developed in accordance with the Standard Protocol Items: Recommendations for Interventional Trials guidelines and the Consolidated Standards of Reporting Trials 2010 statement: extension to randomised pilot and feasibility trials [37–39].

### Trial design

This study is designed as a prospective, parallel group pilot RCT aiming to compare the results of SPN versus IPN for tibial shaft fractures during the first 18 months after surgery. Randomisation will be computer-generated, restricted by stratification, and will be carried out in a 1:1 manner. Randomisation will be stratified by age (< 40/≥ 40) and patient gender.

For every tibial shaft fracture patient enrolled in the RCT, we aim to recruit a healthy, case-matched volunteer from the general population to generate a normative reference dataset. The healthy cohort of volunteers will be case-matched by considering age, sex, height, and body mass, and screened for eligibility over the phone.

### Patient and public involvement

Patients and public were not involved in the design, conduct, or reporting of this study.

### Eligibility

Patients between 18 and 60 years of age will be consented for the study via the surgical team after their admission to the Royal Adelaide Hospital or The Queen Elizabeth Hospital for the treatment of tibial shaft fracture.

### Inclusion criteria

18–60 years old at the time of inclusion;Unilateral, extra-articular, tibial shaft fractures;Intramedullary fixation is the preferred treatment as determined by the treating orthopaedic surgeon.

### Exclusion criteria

Unable to write or read English;Unable to understand spoken English;Unable to give informed consent;Fractures involving the tibial metaphysis (fracture location and limited weight bearing after surgery may affect the outcomes being measured);Other major trauma to the lower limbs (except for ipsilateral fibular fractures);American Society of Anesthesiologists classification of 3 or more at the time of inclusion;Significant pre-existing mobility problems as defined by either:A low [40] (less than seven) New Mobility Score [41] (NMS), orA score of less than two for any individual NMS item.

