### Primary clinical outcome measure

The primary clinical outcome measure for the pilot RCT is the incidence of AKP at 12-months follow-up. To assess AKP, participants will be asked to answer the following questions:

1. Do you experience any pain in the knee of the leg that was operated on? Yes/No

2. Was this pain present only after surgery and not beforehand? Yes/No

3. Is this pain located over the front of your knee? Yes/No

If patients answer yes to all questions, their pain will be regarded as postoperative AKP.

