#### Covariates

##### New mobility score [41] (NMS)

The NMS contains three items pertaining to patients’ ability to walk indoors, outdoors, and go shopping. Each item is scored from 0 to 3, resulting in a score from 0 to 9, where nine indicates a high level of mobility.

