### Exploratory clinical outcomes

The tertiary objective of this study is the development of novel outcome measures specific to IM nailing of tibial shaft fractures from a series of performance-based and patient-reported outcomes captured in the pilot RCT. The successful development of the new tool using a combination of PROMs and PBOMs will be assessed on its ability to differentiate participants with and without AKP.

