As this is a pilot study, any analyses related to the clinical outcomes should be treated with caution and viewed as exploratory. All clinical outcome measures will be assessed descriptively (means and standard deviations for normally distributed continuous variables; medians and interquartile ranges for non-normal continuous variables; frequencies and percentages for categorical variables). Missing data will be tabulated.

Logistic regression models will be used to determine the association between surgical approach and AKP 12 months post-surgery. Models will be adjusted for age and gender with hospital included as a fixed effect. The results will be reported as odds ratios with 95% confidence intervals.

Secondary clinical outcomes will be analysed using linear regression models for continuous outcomes or generalised linear models for count or categorical outcomes. Generalised estimating equations will be used to account for correlation due to repeated measures over time, and a time-by-surgery interaction term will be included to test for differences in the relationship between surgical approach and outcomes over time. If assumptions about distributions are not met (e.g. non-normally distributed continuous outcomes) alternative approaches will be explored as appropriate, including transformations or non-parametric modelling.

To assess differences between cases and matched healthy controls, logistic regression models will be used to determine the association between treatment (surgery versus no surgery) and AKP 12 months post-surgery. Models will be adjusted for the matching variables age, gender, and body mass index, with hospital also included as a fixed effect.

To determine novel predictors of functional outcomes, logistic regression prediction models will be used to assess the discriminatory power of PROMs and PBOMs at assessing AKP and other functional measures. Estimates of discrimination (area under the curve, sensitivity, and specificity) will be used to rank combinations of outcomes in ability to predict AKP. Principal component analysis (PCA) will be explored as a method of data reduction to allow information from a larger number of variables to be included in the predictive model. If PCA is successful, a predictive model will be fitted using an appropriate number of principal components (determined using the proportion of variance explained as well as number of events in the dataset) as predictors.

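### Patients with persisting pre-injury anterior knee pain count as AKP non-cases, so they contaminate the group without AKP used to build and judge the new tool

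*Protocol article*

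**What the plan says.** Inclusion criteria cover age, fracture type ("Unilateral, extra-articular, tibial shaft fractures") and the surgeon's preference for nailing. Exclusion criteria cover language, consent, metaphyseal involvement, other major lower-limb trauma, ASA class and "Significant pre-existing mobility problems as defined by either" a New Mobility Score (NMS) total below seven or any item below two. The Covariates section describes the NMS as covering patients' "ability to walk indoors, outdoors, and go shopping". It has no pain item, and no criterion concerns the earlier state of the knee.

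On the endpoint, the article states: "The primary clinical outcome measure for the pilot RCT is the incidence of AKP at 12-months follow-up". Three yes/no questions define it. The first asks about any pain in the operated knee, and the third asks whether it is at the front. The second asks: "Was this pain present only after surgery and not beforehand? Yes/No". The case rule is: "If patients answer yes to all questions, their pain will be regarded as postoperative AKP".

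Under Statistical analysis, AKP at 12 months enters a logistic regression on surgical approach: "Models will be adjusted for age and gender with hospital included as a fixed effect". No prior-pain term, at-risk restriction or third category is stated. Under Exploratory clinical outcomes, the new tool is to be assessed on its "ability to differentiate participants with and without AKP". Statistical analysis measures this by area under the curve, sensitivity and specificity.

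**The concern.** The eligibility list and the case rule do not fit together. A patient with long-standing anterior knee pain can have the maximum NMS and be enrolled. If that pain is still there at 12 months, the truthful answers are yes, no, yes. The patient is then a non-case, however bad the pain has become.

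Two things are at stake. First, the tool is meant to recognise anterior knee pain from patient-reported and biomechanical data. Patients with a painful anterior knee would sit on the wrong side of its reference standard, and randomisation does nothing to correct that. Second, the AKP incidence and the contrast between approaches are diluted by patients whose answer to the second question is already settled. The Discussion says the clinical outcomes may supply preliminary effect sizes and better power calculations for the full trial, so the dilution would be carried forward.

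**Working it through.** **Inputs from the article.** Target 60 patients, about 25 per group completing (Sample size). 47% of patients reporting AKP in a meta-analysis (Discussion). Absence of AKP of 53% in both groups, a 10-point margin, a two-sided 90% confidence interval and 90% power, giving 1080 patients (Discussion).

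**Assumptions.** Let q be the share of patients whose pre-injury anterior knee pain persists at 12 months and who answer no to the second question. The documents do not give q, so 5%, 10% and 20% are shown. The 47% is applied to the remaining patients. The article does not say that its 47% refers to patients free of earlier pain, and it notes that the assessment method was not detailed.

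**Step 1: the plan's own figure.** Equivalence with both limits and unpooled variance: n per arm = 2 × 0.53 × 0.47 × (1.645 + 1.645)² / 0.10² = 539.2, so 540 per arm and 1080 in total. The figure reproduces and is not in dispute.

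**Step 2: classification.**

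| Patient at 12 months | Q1 pain | Q2 only after surgery | Q3 front | Class |
|---|---|---|---|---|
| New postoperative anterior pain | yes | yes | yes | case |
| Persisting pre-injury anterior pain | yes | no | yes | non-case |
| No knee pain | no | – | – | non-case |

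Rows two and three form one group in the stated analyses.

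**Step 3: incidence and label contamination.** Observed incidence = 0.47 × (1 − q). Share of non-cases with persisting anterior pain: c = q / [1 − 0.47 × (1 − q)].

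| q | Such patients among 50 | Observed incidence | c |
|---|---|---|---|
| 5% | 2.5 | 44.7% | 0.05/0.5535 = 9% |
| 10% | 5 | 42.3% | 0.10/0.577 = 17% |
| 20% | 10 | 37.6% | 0.20/0.624 = 32% |

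**Step 4: effect on the tool.** Suppose a tool flagged every painful anterior knee and nothing else. Measured against the stated labels, its specificity would be 1 − c: about 91%, 83% and 68%. A correct tool would be marked down for being right. This assumes that persisting earlier pain looks to the tool like postoperative AKP.

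**Step 5: effect on the contrast.** Any risk difference is multiplied by (1 − q). For an illustrative 47% v 37% (an assumption), the difference of 10 points (odds ratio 1.51) becomes 9.0 points (1.47) at q = 10% and 8.0 points (1.43) at q = 20%. The total for a superiority comparison at two-sided 5% and 90% power, with variance pooled under the null, rises from 1020 to 1216 and 1462.

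**Step 6: comparison with noise.** With 25 per arm at 47%, the standard error of the difference is √(2 × 0.47 × 0.53 / 25) = 14 points, so the 95% half-width is about 28 points. The attenuation in step 5 is small beside that.

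**The case against.** The strongest case on the other side has four parts.

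- **The second question is deliberate.** It keeps earlier pain from being credited to surgery, and the share of all nailed patients with new AKP is a legitimate target in a trial that follows routine care. This stands: the incidence is too low only if the target is patients free of earlier pain. It does not rescue the tool, whose reference group should not contain painful anterior knees.
- **The information may already exist.** The three answers are recorded separately, a baseline form exists, and the contents of Table 1 are not shown. This stands in part: yes/no/yes responders can be identified at 12 months. But the stated case rule and binary analyses give them the wrong label for the tool. The baseline form is also completed after randomisation, with allocation known. The article says those data are unaffected by allocation, but recall of earlier pain is safer asked beforehand.
- **The size is assumed.** This stands. Both q and the use of 47% as an at-risk rate are assumptions.
- **No pilot decision turns on it.** The progression criteria are about feasibility, and clinical results are labelled exploratory. This limits the weight of the point but does not remove it, because the tool is a stated objective and the effect sizes are meant for the full trial.

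A reader might go further and infer that patients with any earlier knee pain can never become cases. The wording does not support that: someone whose old pain resolved, or who reads the second question as being about a new pain, can answer yes throughout. A reader might also point to chance imbalance. With five such patients, a 4:1 or worse split has probability 2 × [C(25,5) + 25 × C(25,4)] / C(50,5) = 0.35, and a 4:1 split moves the difference by (3/25) × 0.47 = 5.6 points. That is 0.4 of a standard error, and it is ordinary randomisation variation already reflected in the confidence interval.

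**Conclusion.** The point holds as a labelling problem produced by stated rules. No criterion screens for pre-injury knee pain, and the all-yes rule makes a patient with persisting pre-injury anterior pain a non-case. The tool is then built and judged with that patient in the group without AKP. Under the two assumptions (q of 5–20%, 47% AKP in the rest), about 9–32% of that group would have anterior knee pain.

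The effect on the primary clinical outcome is secondary. Observed incidence would be 44.7–37.6% instead of 47%, and the difference between approaches would shrink by 5–20% of its size. Randomisation equalises q between arms in expectation, so there is no systematic bias toward either approach. At the lower end of the range the effect is minor beside the imprecision of 50 completers.

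The documents do not support concluding that such patients should be barred from entry. Excluding anyone with earlier disease or surgery of either knee would also remove pain-free patients who are fully at risk of the outcome, in a pilot that already calls its enrolment rate unpredictable.

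**What to change.** Leave the entry criteria as they are, and make three changes.

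1. **Baseline question.** Before the allocation envelope is opened, ask whether the patient had pain at the front of the index knee before the injury. Refer to the injury and not the operation, because the existing second question is anchored on surgery.
2. **Tool analyses (Exploratory clinical outcomes; Statistical analysis).** Leave yes/no/yes responders out of the reference group without AKP, and report them as a separate category when the tool is built and judged.
3. **12-month AKP (Statistical analysis).** Report incidence and the approach model in patients free of pre-injury anterior knee pain, alongside the all-randomised analysis. Define this subset by the baseline question and not by the 12-month answers. Because the item precedes allocation, the restricted comparison remains a randomised one.

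The cost is one extra question and a slightly smaller denominator for the at-risk and tool analyses: at the assumed 5–20%, about 3–12 of 60 enrolled, or 2.5–10 of 50 completers. Recruitment to 60 is unaffected.

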### Randomisation and blinding

Consenting patients will be randomised into either SPN or IPN groups by a member of the surgical team through revealing allocation cards inside concealed envelopes. A randomly permuted blocks schedule was created with two treatment arms (labelled A and B) with equal allocation over four strata (males under 40, females under 40, males 40 and over, females 40 and over). Two block sizes (2 and 4) were used and allocated in equal proportions. A unique, non-informative, 3-digit study subject identifier was generated for each treatment allocation. Fifty allocations were generated per stratum with a total of 200 allocations. This process was replicated for each study site resulting in two unique schedules. The randomisation schema was generated by a University statistician using Stata v15.1 (StataCorp LP, College Station, TX, USA) and the user-written Stata package ralloc [42]. The concealment of allocation cards was performed by researchers outside of the surgical team who will enrol patients and reveal the allocations. Due to the nature of the surgical intervention, patients, surgeons, and researchers will not be blinded to the randomisation allocation as participants will acquire scars at different sites.

